### Statistics - clinical

Continuously collected physiological data (e.g. heart rate, SpO_2_, respiratory rate) will be summarised as area under the curve (AUC) in 24 h epochs. A cumulative AUC for the first 21 days will be calculated for each participant, and the mean ((± standard deviation, SD) of this variable compared between the two dosages (1.0 mg/kg 48-hourly in Stage 1 and up to 1.5 mg/kg 24-hourly in Stage 2).

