### Exclusion criteria

• Inability of the legal guardians to consent.• Any disease or condition that the investigators judge could confound the trial results; these include, but are not limited to, genetic syndromes, severe cardiac or other abnormalities, substantial pre-/perinatal compromise (postnatal hypoxia (SaO2<80% for >3h), intrauterine stroke and others.• Imminent death.• Foreseeable inability to adequately excrete anakinra, i.e. severely and permanently compromised renal function.

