### Summary dosing strategy

For Stage 1, six infants will receive 1.0 mg/kg IV given alternate daily from day 1 to day 21 after birth. In the event of acute kidney injury (AKI), detection during blood monitoring within the 3 weeks of treatment, anakinra treatment will be halted until renal function has recovered as defined below.

After completion of Stage 1, the Investigators and the data safety monitoring board (DSMB) will conduct an interim analysis, including assessment of mortality and rate of complications of prematurity, and comparison of observed exposure with the predicted exposure estimated from the population PK simulation. If appropriate, with confirmation of mature non-renal clearance within the first cohort of 6 infants, Stage 2 will administer 1.5 mg/kg per day for the remaining 18 infants. Furthermore, dosing will not need to be withheld in the setting of acute kidney injury (AKI) if non-renal clearance is confirmed to be mature from birth.

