### Safety monitoring

All participating infants will be monitored closely following the infusion of anakinra as is standard clinical practice at Monash Children’s Hospital’s Neonatal Intensive Care Unit (NICU) and most other NICUs, with particular attention to vital signs in the 10 min immediately after the administration of anakinra. Adverse event (AE) reporting will be commensurate with the clinical course expected for the study population of extremely preterm infants.

Adverse Events are defined as:

• Any untoward medical occurrence in a patient enrolled into the study• Sustained unexpected change of 30% or more from baseline vital signs (heart rate, blood pressure, respiratory rate, oxygen saturation, body temperature) within 10 min of anakinra administration• Unexpected need to escalate respiratory support within 12 h of anakinra administration• Unexpected need to initiate or escalate inotropic support within 12 h of anakinra administration• Any event requiring cardiopulmonary resuscitation that occurs within 12 h of anakinra administration will be investigated as a potential serious AE.

To assess safety, the following monitoring will be conducted:

1. Early respiratory outcomes will comprise mode of ventilation, lowest pH, highest pCO_2_, highest FiO_2_ and highest mean airway pressure or continuous positive airway pressure (CPAP) level. The respiratory index will be calculated from the last 2 items. Each of these parameters will be recorded daily for the entire treatment duration, and on postnatal day 42. We will also record:

a) each intubation event up to postnatal day 42, including the reason for intubation (e.g. FiO_2_ requirement, respiratory acidosis, apnoea, other);b) surfactant administration (number of doses);c) administration of inhaled nitric oxide (yes/no);d) maximum maintenance caffeine dose used (mg/kg/day).

For analysis purposes, we will further record:

e) Maternal clinical data from the ante- and peri-natal period, including duration of rupture of membranes, maternal fever, chorioamnionitis, antibiotic therapy, maternal medication (including antenatal steroids and magnesium sulfate), hypertension, gestational diabetes, abnormalities of antenatal ultrasounds, and other conditions relevant to the wellbeing of the infant; andf) mode of delivery, Apgar score and resuscitation.

2. Later cardiopulmonary outcomes will comprise duration/last day receiving of:

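### The planned AUC of heart rate, SpO2 and respiratory rate averages highs against lows, so the between-dosage comparison is insensitive to instability; time outside pre-set limits should carry it instead.

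*Protocol article*

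**What the plan says.** In the protocol article, the section Statistics - clinical covers "Continuously collected physiological data (e.g. heart rate, SpO_2_, respiratory rate" and states that these "will be summarised as area under the curve (AUC) in 24 h epochs". It continues: "A cumulative AUC for the first 21 days will be calculated for each participant". The mean (SD) is then "of this variable compared between the two dosages". The section names no reference level, target band, time outside limits or measure of variability, so the natural reading is the AUC of the raw signal.

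The groups being compared are the six Stage 1 infants and the rest: "Stage 2 will administer 1.5 mg/kg per day for the remaining 18 infants" (Summary dosing strategy).

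Three other places bear on the point:

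- Exclusion criteria gives as an example of substantial compromise "postnatal hypoxia (SaO2<80% for >3h", which is a time below a limit.
- Safety monitoring counts as an adverse event a "Sustained unexpected change of 30% or more from baseline vital signs", but only within 10 min of a dose. It also lists any untoward medical occurrence, unexpected escalation of respiratory or inotropic support within 12 h of a dose, and resuscitation within 12 h.
- Safety monitoring also records daily "lowest pH, highest pCO_2_, highest FiO_2_ and highest mean airway pressure" or CPAP level, and every intubation to day 42 with its reason.

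**The concern.** Each of these signals can go wrong in both directions: bradycardia and tachycardia, hypoxia and hyperoxia, apnoea and tachypnoea. A summary that averages over the day treats a low spell and a later high spell as cancelling. It also spreads a short spell over 24 h, and then over 21 days. Two infants with very different courses can have nearly the same value.

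The weakness lies inside each 24 h epoch. Complete recordings, normalised epochs and adjustment for covariates would not remove it.

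At stake is how informative the article's one stated comparison of continuous vital signs between dosages can be. If the higher dosage made infants less stable without moving their average level, this comparison would be poorly placed to show it.

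**Working it through.** The plan gives no figure for this point, so there is none to reproduce. The inputs from the article are the 24 h epoch, the 21-day total (21 × 24 = 504 h), the group sizes of 6 and 18, and the exclusion example of saturation below 80% for more than 3 h. All vital-sign levels below are assumptions chosen for illustration, and a range is shown where it matters.

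**1. Identity.** AUC over 24 h = 24 × time-weighted mean. If an infant spends h hours at a low level L, the level x in the remaining hours that gives the same AUC as a stable infant at S is

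x = (24·S − h·L) / (24 − h).

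**2. Offsetting within one day.**

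| Signal | Stable day | Unstable day |
|---|---|---|
| SpO2 (%·h) | 24 × 92 = 2208 | 6 × 80 + 18 × 96 = 2208 |
| Heart rate (/min × h) | 24 × 150 = 3600 | 6 × 90 + 18 × 170 = 3600 |
| Respiratory rate (/min × h) | 24 × 50 = 1200 | 6 × 20 + 18 × 60 = 1200 |

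If the SpO2 pattern were repeated for 21 days, 126 h at 80% plus 378 h at 96% would equal 504 h at 92%.

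**3. The article's own marker of hypoxia, taken as 3 h at 79%.** The other 21 h must average:

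- stable level 92%: (2208 − 237) / 21 = 93.9%
- stable level 95%: (2280 − 237) / 21 = 97.3%
- stable level 96%: (2304 − 237) / 21 = 98.4%

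The exclusion criterion is worded in SaO2 and the planned summary in SpO2; they are treated as comparable here.

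**4. Limit set by the 100% ceiling.** With the remaining hours at 98%, the hours at 80% that leave the daily AUC unchanged are 24 × (98 − S) / (98 − 80):

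| Stable level S | 90% | 92% | 94% | 95% | 96% |
|---|---|---|---|---|---|
| Hours at 80% | 10.7 | 8.0 | 5.3 | 4.0 | 2.7 |

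Against a stable 96%, 6 h at 80% would need x = (2304 − 480) / 18 = 101.3%, which is impossible. Heart rate and respiratory rate have no such ceiling.

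**5. Dilution with no compensating highs.**

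- SpO2, 6 h at 80% against 93%: the loss is 6 × 13 = 78 %·h. That is 78 / (24 × 93) = 3.5% of the day and 78 / (504 × 93) = 0.17% of the 21-day value.
- Heart rate, 6 h at 90 against 150: the loss is 6 × 60 = 360. That is 360 / 3600 = 10% of the day and 360 / (504 × 150) = 0.48% of the 21-day value.

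**6. What the adverse event rule adds.** A 30% fall from 92% means SpO2 of 0.70 × 92 = 64.4% or lower, so a fall to 80% (12 / 92 = 13%) does not qualify. A heart rate falling from 150 to 90 (40%) would qualify, but only inside the window. With 21 daily doses in Stage 2, the windows total 21 × 10 min = 3.5 h, which is 3.5 / 504 = 0.7% of the treatment period.

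**7. The alternative summary on the same example.** For any lower limit above 80% and not above 92%, the unstable SpO2 day in step 2 scores 6 / 24 = 25% of time below the limit and the stable day scores 0%. A single such day among 21 still contributes 6 / 504 = 1.2% against 0%.

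**The case against.** **Nothing decisive rests on this AUC.** This stands. Safety is defined by completing the regimen without adverse events beyond those expected (Definitions, Safety). The move to Stage 2 rests on mortality, complications of prematurity and observed against predicted exposure (Summary dosing strategy). The DSMB reviews adverse incidents and the PK analysis. A reader might infer that equal AUCs would be taken to show no physiological effect of dose, but the article does not say so.

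**Much instability is caught elsewhere.** This stands in part. Safety monitoring picks up acute changes after a dose, escalation of support, intubations with reasons such as apnoea, and daily worst blood gas and support values. A reader might infer that the trial is blind to cardiorespiratory harm, and that would be wrong. What is missing is narrower: none of these items is time spent in hypoxia or bradycardia over the whole day.

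**The exact ties are constructed.** This also stands. A difference of exactly zero arises only when levels and durations are chosen to match, and none of those levels comes from the article. It would be too strong to say that the AUC cannot register instability. Where highs do not fully compensate it moves, though by little (step 5), and it responds to a sustained shift in the mean.

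**The full protocol or SAP may define the AUC relative to a limit.** This is possible, and an article need not give every detail. But the article does commit to a summary measure, without a threshold, and a between-dosage comparison based on it. The point concerns that stated choice.

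**Conclusion.** The concern holds as a limited one. As written, the article's comparison of continuous vital signs between dosages is insensitive to instability, because an unthresholded AUC is a mean multiplied by time. Under the assumed levels, between 2.7 h (stable 96%) and 10.7 h (stable 90%) at SpO2 80% can leave the daily AUC unchanged when the rest of the day is at 98%. An uncompensated 6 h spell moves the 21-day value by 0.17% for SpO2 and 0.48% for heart rate.

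The conclusion assumes that AUC means the area under the raw signal. It does not depend on variance, power or group size. It does not extend to the trial's primary safety conclusion, the dose decision or safety monitoring as a whole.

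**What to change.** In Statistics - clinical, add for each signal the percentage of monitored time below a lower limit and above an upper limit. Average each over the infant's monitored treatment days and make these the between-dosage comparison. Keep the AUC or mean as description of level. The investigators should fix the limits before the data are analysed; they serve the analysis only and do not change care.

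This uses the same recordings and needs no extra infants or procedures. The costs are:

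- a little more programming;
- agreement on the limits in advance;
- a few more descriptive comparisons in 6 versus 18 infants: for the three named signals, two directions each give 3 × 2 = 6, in place of 3 AUC comparisons.

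Replacing AUC with episode counts and within-epoch SD as well would go further than the article supports. Both depend on the recording resolution, which it does not state, and a larger set of daily summaries would need its own aggregation rule.

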### Sample size

We will recruit 24 infants. Given the well-established, favourable safety profile and extensive clinical experience with anakinra, including in children and infants, as well as detailed knowledge on its mechanism of action, this number of participants will suffice to demonstrate safety and feasibility. In addition, it will allow confirmation of predicted/simulated drug disposition, by comparing observed concentration with the population PK simulation, to inform dose selection for future large effectiveness trials.

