### Definitions

#### Safety

For the purposes of the trial’s primary objective, safety will be defined as completion of the described treatment regimen in our target population, without any adverse events of greater frequency or severity than expected to be observed in this high-risk population. For example, at Monash Newborn the baseline rate of late-onset sepsis in this population is 27%, early-onset sepsis is 1%, death is 15%, BPD is 70% and necrotising enterocolitis is 12%.

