### Estimated duration of individual subject participation

Anakinra treatment commences at 3-24 hours of postnatal life and ceases on postnatal day 21. Treatment will continue until day 21 unless one of the following occurs: a suspected unexpected serious adverse reaction; acute kidney injury (which would increase dose-normalised exposure in the unlikely setting of immature non-renal clearance); neutropenia; or elevation of liver enzymes (details below). To monitor for these events and as part of standard care, the following blood tests will be sent to the routine pathology laboratory on days 1, 3, 7, 14, and 22 after starting IL-1Ra infusions in addition to plasmatic and cellular immunity analysis: full blood count, liver enzyme tests, urea, electrolytes and creatinine.

Treatment will cease if consent is withdrawn, in which case consent will be sought for the infant to remain enrolled and data collection to continue to enable intention-to-treat analysis. Rates of withdrawal of consent will be monitored to detect differential dropout, which can bias clinical trial results and reduce the power of the trial to detect important differences. Treatment will also cease if death is imminent and the treating team with the parents have made the decision to redirect care.

Collection of data will continue until 2 years of age, with a review at 3 months corrected age (i.e. 3 months after the infant reaches an age that equates to 40^0^ weeks GA) in the Early Neurodevelopmental Clinic (including a Prechtl’s general movements assessment), and a neurodevelopmental review at 2 years.

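### The between-dose comparison of vital signs uses a 21-day cumulative AUC that is not divided by time observed, so an early death or incomplete recording lowers a stage's mean whatever the physiology

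*Protocol article*

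**What the plan says.** The Statistics - clinical section of the protocol article consists of one analysis. Continuously recorded signs, with heart rate, SpO2 and respiratory rate as examples, "will be summarised as area under the curve (AUC) in 24 h epochs". These are then accumulated: "A cumulative AUC for the first 21 days will be calculated for each participant, and the mean" (with standard deviation) "of this variable compared between the two dosages". The section states no division by hours observed. It names no hypothesis test, significance level or target difference.

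The group sizes come from Sample size and Summary dosing strategy: "We will recruit 24 infants", of whom six form Stage 1 ("For Stage 1, six infants will receive 1.0 mg/kg IV given alternate daily from day 1 to day 21 after birth") and the rest Stage 2 ("Stage 2 will administer 1.5 mg/kg per day for the remaining 18 infants").

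The protocol expects that some infants will not survive. Its Safety definition gives local baseline rates, among them "early-onset sepsis is 1%, death is 15%, BPD is 70% and necrotising enterocolitis is 12" per cent, with no time window on the death rate. The section on duration of participation foresees deaths during treatment: "Treatment will also cease if death is imminent and the treating team with the parents have made the decision to redirect care".

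**The concern.** A cumulative AUC carries two quantities at once: the level of the vital sign and the time over which it was recorded. Only the first is of physiological interest. When every infant is observed for the full 21 days the second is constant and harmless. When some are not, the stage mean moves with survival and recording completeness.

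The direction is also awkward. A stage with more early deaths shows a lower cumulative heart rate, which could mask a real rise or look like a fall. This is the only between-dose clinical comparison the section states, and the trial is meant to inform dose selection for later trials, so readers are likely to look at it.

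**Working it through.** The plan gives no power, effect size or SD for this comparison, so there is no figure of its own to reproduce.

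**Inputs from the protocol article.** Stage 1 n = 6; Stage 2 n = 18; window 21 days; baseline mortality 15%, undated.

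**Assumptions, not in the documents.** The AUC is taken from zero and stops at death. Between-infant mean (SD): heart rate 155 (8) bpm, SpO2 92 (2) %, respiratory rate 50 (8) per minute. Deaths by day 21: 2% to 15% of infants, at times uniform over days 1 to 21.

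**Step 1: shift from one death on day 7.** With the same vital-sign level in every infant, the level cancels and only days count.

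- Stage 1: (5 × 21 + 7) / (6 × 21) = 112/126 = 0.889, a fall of 11.1%.
- Stage 2: (17 × 21 + 7) / (18 × 21) = 364/378 = 0.963, a fall of 3.7%.

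These two figures need no assumption about the vital signs. In heart-rate terms at 155 bpm, they match a rate lower by 155 × 0.111 = 17.2 bpm in all six Stage 1 infants for 21 days, or by 155 × 0.037 = 5.7 bpm in all 18 Stage 2 infants.

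**Step 2: can the sign reverse?** Suppose the true level is 155 bpm in Stage 1 and 165 in Stage 2, with no Stage 1 deaths and two day-7 deaths in Stage 2. On a per-hour scale the Stage 2 mean becomes 165 × (16 + 2 × 7/21)/18 = 152.8, below 155. A true 10 bpm rise then appears as a fall.

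**Step 3: how likely is a death by day 21?** P(at least one of 24) = 1 − (1 − p)^24.

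| Deaths by day 21 (assumed) | P(at least one of 24) |
|---|---|
| 2% | 38% |
| 5% | 71% |
| 10% | 92% |
| 15% | 98% |

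**Step 4: how much of the spread is time observed?** Let f be the fraction of 21 days observed, μ the mean level and σ the between-infant SD. With level independent of f, the share of variance due to time is μ²Var(f) / [μ²Var(f) + σ²E(f²)]. At 5% deaths E(f²) = 0.9675 and Var(f) = 0.01455. For heart rate this gives 155² × 0.01455 = 349.6 against 64 × 0.9675 = 61.9, a share of 85%.

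| Deaths by day 21 | Heart rate | SpO2 | Respiratory rate |
|---|---|---|---|
| 2% | 69% | 93% | 19% |
| 5% | 85% | 97% | 37% |
| 10% | 92% | 98% | 54% |
| 15% | 94% | 99% | 64% |

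A simulation of 6 v 18 infants agrees with this table at 5%, 10% and 15%. Varying the heart-rate SD from 5 to 12 bpm and deaths from 2% to 15% moves the heart-rate share between 50% and 98%. Respiratory rate is less affected because its assumed spread is large relative to its mean (8/50 = 16%, against 8/155 = 5% for heart rate and 2/92 = 2% for SpO2).

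**Step 5: no deaths, but recording gaps.** With gaps averaging 5% of the time (0 to 10%), the simulated share is 26% for heart rate, 66% for SpO2 and 4% for respiratory rate. With no deaths and no gaps it is zero.

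**The case against.** The best defence is that nothing in the trial turns on this variable. Safety is judged by adverse-event frequency and severity against expected rates, feasibility by completion of the course, and Stage 2 dosing by the investigators and the data safety monitoring board from mortality, complications and observed versus predicted exposure. Deaths would not go unseen, since mortality is assessed explicitly between the stages. This stands, and it limits the severity.

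A second defence is that an unseen analysis plan may hold rules for deaths and gaps. That covers missing detail, but here the protocol article itself fixes the variable as a cumulative AUC; a later document would have to replace it, not merely supplement it. The article also does not state the AUC's reference level. Level times hours is the natural reading, but it is an inference.

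Several stronger readings are tempting and not supported:

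- A reader might infer that the comparison loses a stated amount of power. No test is planned, so any power figure would describe an analysis of the reader's own making, with assumed heart rates and death times.
- A reader might infer that the measure mainly records survival for every sign. That fails for respiratory rate at low death rates, and for all signs if everyone is fully observed. Enrolled infants may also die less often than the 15% suggests, because imminent death and substantial perinatal compromise are exclusions.
- A reader might treat monitor gaps like a day-7 death. A gap costs only its own share of the 21 days.
- A reader might add the absence of gestational-age adjustment. That is a separate analysis choice that would apply equally to a time-averaged mean, and one commonly left to an analysis plan.

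**Conclusion.** The point holds, at moderate weight. As written, the between-dose summary mixes vital-sign level with time observed. The shifts of 11.1% (Stage 1) and 3.7% (Stage 2) per day-7 death follow from the group sizes and the 21-day window, given an AUC taken from zero that stops at death. How often such a shift will occur depends on deaths by day 21, which the documents do not give: over an assumed 2% to 15%, the chance of at least one among 24 infants is 38% to 98%. The effect is largest for SpO2 and heart rate and weaker for respiratory rate, and it vanishes with full survival and complete recording. It does not undermine the trial's safety, feasibility or escalation decisions. It does make the one stated between-dose clinical comparison hard to interpret.

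**What to change.** Replace the cumulative AUC with the time-weighted mean, that is, the AUC divided by monitored hours. Alternatively, analyse the 24-hour epoch means (not epoch sums, which have the same fault when an epoch is partly recorded) in a repeated-measures model with stage and postnatal day as terms and infant as a random effect. Report deaths by stage next to the result.

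The time-weighted mean has a small downside. For an infant who dies it reflects only early days and pre-death physiology, and is then compared with survivors' full three weeks. It should therefore be accompanied by the day-adjusted epoch analysis or by a sensitivity analysis in survivors to day 21.

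The cost is a wording change in the protocol or analysis plan. It uses data already to be collected and needs no additional infants or procedures.

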### Study type

Investigator-initiated single-arm, Phase I/IIa dose-escalation safety trial.

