### Inclusion criteria

• Born between 24^0^ and 27^6^ weeks of GA• Born at on-site at the participating hospital.

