However, if this predicted optimal dosing rate of 1.5 mg/kg daily were used from the start and non-renal clearance were immature, this dosing rate would lead to excessive exposure, beyond that seen in older children receiving 3 mg/kg daily of anakinra. This eventuality is avoided with the planned staged approach, in which the first 6 participants receive 1 mg/kg alternate daily, followed by interim PK analysis. The rationale for this decision is as follows. Keeping the threshold of 9.6 mg/l x h in mind beyond which sufficient anti-inflammatory activity can be expected (28), **Figure 3** depicts simulations in studied populations (A-E) and extrapolated populations (F-I), with F and G depicting the predicted exposure if non-renal clearance is fully mature, H and I if non-renal clearance is only 25% mature. Assuming mature non-renal clearance, the stage 1 dosing regimen of 1 mg/kg alternate daily predicts exposure equivalent to 1 mg/kg in a child weighing 12 kg, whilst Stage 2 (optimal) dosing of 1.5 mg/kg daily predicts exposure equivalent to 3 mg/kg in a child of 12 kg. Interim analysis after the first six participants will allow confirmation of non-renal clearance being mature, and enable safe progression to the 1.5 mg/kg daily dosing schedule. On the other hand, in the unlikely case that non-renal clearance is immature (for example at 25% maturity), the initial dosing regimen of 1 mg/kg alternate daily will lead to exposure close to that seen with dosing rate of 3 mg/kg daily in an older child. If non-renal clearance were found to be immature at interim analysis, dosing in Stage 2 would be adjusted accordingly.

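### The only stated comparison of the two doses sets raw means for the first 6 infants against the next 18, which leaves it open to confounding by gestational age

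*Protocol article*

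**What the plan says.** The article calls the study an "Investigator-initiated single-arm, Phase I/IIa dose-escalation safety trial" (Study type). On numbers it says "We will recruit 24 infants" (Sample size). Dose is fixed by order of entry: "the first 6 participants receive 1 mg/kg alternate daily, followed by interim PK analysis" (Dose selection, d) Simulations), and then, if the interim review supports it, "Stage 2 will administer 1.5 mg/kg per day for the remaining 18 infants" (Summary dosing strategy).

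The section Statistics - clinical defines one analysis. Continuous physiological signals are reduced to a cumulative AUC over the first 21 days for each infant, and the mean (SD) is to be "of this variable compared between the two dosages (1.0 mg/kg 48-hourly in Stage 1 and up to 1.5 mg/kg 24-hourly in Stage 2"). It names no model, test, interval or covariate.

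The only gestational-age restriction is eligibility: "Born between 24^0^ and 27^6^ weeks of GA" (Inclusion criteria). The article describes no stratification or other balancing between stages.

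Two statements bear on a pre-dose value. The adverse-event definitions include a "Sustained unexpected change of 30% or more from baseline vital signs (heart rate, blood pressure, respiratory rate, oxygen saturation, body temperature") within 10 minutes of a dose (Safety monitoring). On timing: "Anakinra treatment commences at 3-24 hours of postnatal life and ceases on postnatal day 21" (Estimated duration of individual subject participation).

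**The concern.** Which infant receives which regimen depends only on when the infant is enrolled. A difference in mean AUC between stages can then reflect the maturity of the infants who came first as well as the dose. Gestational age is the obvious candidate: it is the characteristic that defines the population, it may vary by almost four weeks, and it is recorded for all 24 infants. A contrast of raw means makes no use of it.

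The stake is limited but real. The Sample size section says the trial should inform dose selection for later effectiveness trials, and this is the one place where the article sets the two doses side by side on clinical data. With six infants in one group, an imbalance in maturity could be read as a dose effect or could hide one.

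**Working it through.** **The plan's own figure.** Stage 1 has 6 infants and Stage 2 has 18; 6 + 18 = 24, which matches the stated sample size. The article gives no alpha, power, effect size, SD or correlation, so there is no power statement to reproduce. Two-sided 5%, a 1 SD difference and all correlations below are assumptions.

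**Is it the only between-dose comparison?** The interim pharmacokinetic analysis compares observed with predicted exposure (Secondary objectives; Summary dosing strategy). Primary safety is judged against expected background rates (Definitions, Safety). Neither compares the doses, so the AUC comparison is the only one stated.

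**How far can gestational age differ between stages?** Assume it is uniform from 24 weeks 0 days to 27 weeks 6 days.
- Range: 27.857 − 24 = 3.857 weeks. SD = 3.857/√12 = 1.113 weeks.
- SE of the difference in stage means = 1.113 × √(1/6 + 1/18) = 1.113 × 0.4714 = 0.525 weeks.
- P(difference above 0.5 week) = 2 × P(Z > 0.5/0.525) = 34% (simulation from the uniform distribution: 35%).
- P(difference above 1 week) = 2 × P(Z > 1/0.525) = 6% (simulation: 6%).

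These are chance imbalances. A drift in case mix over the roughly 24 months of enrolment would add to them.

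**What would a 1-week imbalance do?** The shift in the dose contrast, in SDs of the AUC, is r × 1/1.113, where r is the correlation of gestational age with the AUC.
- r = 0.2: 0.18 SD
- r = 0.3: 0.27 SD
- r = 0.5: 0.45 SD

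The SE of the raw contrast is 0.47 SD, so the last value is about one standard error.

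**What does adjustment cost or gain?** With k covariates, df = 22 − k, and in SD units SE = √[(1 − R²) × (1 + k/(df − 1)) × (1/6 + 1/18)], with no inflation term when k = 0. Half-widths are t(0.975, df) × SE. Power is from the noncentral t distribution.

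| Analysis | 95% CI half-width (SD) | Power for 1 SD |
|---|---|---|
| Unadjusted, df 22 | 0.98 | 53% |
| Gestational age, R² = 0, df 21 | 1.005 | 51% |
| Gestational age, r = 0.3 (R² = 0.09) | – | 54% |
| Gestational age, r = 0.4 (R² = 0.16) | – | 58% |
| Gestational age, r = 0.5 (R² = 0.25) | 0.87 | 63% |
| Two covariates, R² = 0, df 20 | 1.03 | 48% |
| Two covariates, R² = 0.09 | – | 52% |
| Two covariates, R² = 0.25 | – | 60% |

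Break-even R², where the adjusted half-width equals the unadjusted one, is 1 − [t(0.975, 22)/t(0.975, df)]²/(1 + k/(df − 1)). This gives about 0.05 for one covariate and about 0.11 for two.

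**The case against.** **The article is silent on adjustment and does not rule it out.** Covariates are often left to an analysis plan, and antenatal and perinatal data are recorded for analysis purposes. This limits the point. What remains is that the article does state a contrast, of means by dosage, and that contrast is weak for groups formed by enrolment order.

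**The comparison carries no stated decision.** Safety is judged against background rates, and Stage 2 dosing is agreed before Stage 2 data exist. This stands, and it is why the result should be labelled descriptive. The power figures above only price the adjustment; the article plans no test.

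**A reader might infer that the comparison is confounded.** The documents do not show that. The 34% and 6% are chance imbalances that would arise equally under randomisation to 6 and 18, and an ordinary standard error already allows for them. No systematic difference in gestational age between stages is documented, and no correlation with the AUC is given. What holds is that nothing in the design prevents such a difference.

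**A reader might also infer that leaving out covariates loses precision.** That depends on an unknown correlation. Below an R² of about 0.05, adjusting for gestational age costs a little precision.

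**Pre-dose vital signs look like a natural second covariate.** The documents do not establish that they are usable. The baseline in the adverse-event definition concerns the minutes around any dose. The time before the first dose varies from 3 to 24 hours, and those hours may fall inside the 21-day AUC, so the covariate could be part of the outcome. Two covariates also break even only at R² of about 0.11.

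**Adjustment does not separate dose from calendar period.** True: stage and period coincide, and no covariate can separate them.

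**Conclusion.** The point holds as a vulnerability in the stated method. The one between-dose comparison contrasts raw means from 6 and then 18 consecutive, non-randomised infants, and ignores a covariate known for every infant. Under the uniform assumption, the stages differ in mean gestational age by more than half a week about one time in three, and by more than a week about one time in eighteen. Whether that would distort the AUC contrast materially depends on a correlation the documents do not give: a 1-week imbalance moves it by 0.18 to 0.45 SD for correlations of 0.2 to 0.5.

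The case for adjustment rests on guarding against an imbalance in maturity. A gain in precision is possible but not assured. The comparison is secondary and no stated rule depends on it, so this is a modest improvement to the analysis and does not threaten the trial's primary conclusion.

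**What to change.** Amend Statistics - clinical as follows:
- Keep the stage means (SD) of the cumulative AUC. Beside them, report the Stage 2 minus Stage 1 difference with a 95% confidence interval from a linear model containing stage and gestational age at birth (continuous).
- Label the comparison descriptive.
- State that stage coincides with calendar period, so an adjusted difference cannot be attributed to dose alone.
- Add a pre-dose vital-sign covariate only if a window before the first dose is defined, is available for all infants and is excluded from the outcome AUC.

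For the gestational-age adjustment the cost is a change of wording and one of 22 degrees of freedom. It needs no extra infants, samples or data, because gestational age is already an eligibility item. If gestational age proves unrelated to the AUC, the half-width of the interval grows from 0.98 to about 1.005 SD.
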